#### Subgroup analyses

Age is considered a key moderating factor on the effects of recovery from TSR^44^ and it informs surgeons’ clinical decisions about whether to perform aTSR or rTSR. We therefore will directly compare aTSR and rTSR in two specific subgroups, for differential treatment effects: age 60–69 years (where the two surgical approaches are carried out in approximately even numbers in routine practice), and 70+years (where clinically, rTSR is generally given more commonly than aTSR). We shall include an interaction term between age and treatment group in the primary analysis model and shall also model the primary outcome in each of the two subgroups separately. We anticipate that rTSR will have increased effectiveness over aTSR in participants aged 70+years than in younger patients.

#### Additional analyses

There is the potential for participants in this trial not to receive their allocated intervention (eg, surgery not performed, or they cross over from one treatment arm to the other). A complier average causal effect (CACE) analysis will be carried out at the 24-month time-point to account for this. Compliers are defined as participants who received their allocated TSR. The CACE analysis will be implemented using a two-stage least squares instrumental variable approach with randomised treatment assignment as the instrument variable and the received allocated TSR as the exogenous variable.^45^ The linear regression model will control for age, gender and baseline total SPADI score.

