#### Interventions

For both interventions, we will only include commercially available, off-the-shelf implants. We define ‘off the shelf’ as not designed or bespoke but taken from existing stock or supplies. Some hospitals will use fluoroscopic imaging during surgery, as part of their standard practice.

To reflect the pragmatic design of this trial, a required level of experience of the operating surgeon will not be defined, although all surgeons performing TSR for patients within the trial will be required to be familiar with the techniques and equipment that they are using. Data will be collected on the grade and experience of the primary and secondary surgeons through the NJR minimum data set.

The treatment of the rotator cuff during the surgical approach and repair on completion of the surgery will be recorded but will be left to the discretion of the operating surgeon. The surgical approach may include a deltopectoral or deltoid splitting approach and will depend on local practice at recruiting sites. This will not be mandated in the protocol in keeping with the pragmatic design but will be recorded. There may be some patients who are initially randomised to aTSR whose rotator cuff is deemed unsuitable at surgery and thus receive rTSR instead. These patients will be followed up under intention-to-treat and the incidence of these crossovers will be monitored throughout. Figure 2 illustrates the two types of TSR that are described below.

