#### Primary outcome

The primary outcome is the total pain and disability score measured using the SPADI at 24 months. The 13-item SPADI is a validated and sensitive instrument for use in TSR that assesses two domains: pain (five items) and functional activities (eight items) on numerical rating scales.^15 18^ The total score ranges from 0 to 100 where 0 indicates no shoulder pain or disability and 100 indicates worst possible shoulder pain or disability.

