### Sample size

The primary outcome is the total SPADI score at 24 months. As our trial compares two active treatments, we expect a relatively small difference in SPADI score between groups at 24 months, so our target difference between the rTSR and aTSR groups is eight points (the smallest published, validated difference classed as clinically important).^34^ We also conservatively assumed a group SD of 25 points, based on three non-randomised studies.^35^,^37^ We plan to use a linear mixed-effects model in the primary outcome analysis, but due to a paucity of data in the literature to inform our between-measurement correlations, we instead calculate the sample size estimate based on an ANCOVA (‘baseline-as-a-covariate’) model.

Assuming a baseline/24-month SPADI score correlation of 0.35,^38^ 182 participants per group (364 total) are required to give 90% power to detect a difference of at least eight points (SD 25) between aTSR and rTSR, and a 5% significance level. Allowing for 15% loss to follow-up at 24 months,^39^ we aim to randomise a total of 430 participants.

The OSS is our key secondary outcome measure allowing direct comparison of the trial population to those in the NJR in order to explore external validity of the trial sample. Assuming a between-group difference of 2.7 points on the OSS, an expected SD of 8.80, and a baseline correlation of 0.35, the sample size of 430 would achieve 87.5% power using a similar ANCOVA analysis method and the same underlying assumptions.

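### The CACE two-stage least squares uses receipt of the allocated implant as its treatment variable, so the first stage measures the adherence gap between arms and the estimate is not a CACE

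*Protocol article*

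**What the plan says.** Under Additional analyses, the protocol article recognises that some participants will not get the allocated operation ("surgery not performed, or they cross over from one treatment arm to the other") and plans a CACE analysis at 24 months to account for this. It gives this definition: "Compliers are defined as participants who received their allocated TSR". The method is two-stage least squares, "with randomised treatment assignment as the instrument variable and the received allocated TSR as the exogenous variable", adjusted for age, gender and baseline total SPADI.

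The Interventions section says where crossover is expected: "There may be some patients who are initially randomised to aTSR whose rotator cuff is deemed unsuitable at surgery and thus receive rTSR instead". The Sample size section describes the comparison in these terms: "As our trial compares two active treatments". No section gives an expected crossover or adherence rate, and none recodes the treatment variable as the type of implant received.

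**The concern.** Coding the treatment variable as adherence suits a trial in which only one arm can receive the treatment: in the control arm the variable is then zero, and the first stage is the uptake rate. Here, receiving the allocated TSR is possible, and likely, in both arms. The variable is near 1 in each, and allocation shifts it only by the amount that adherence differs between arms. Dividing the ITT effect by that small difference inflates it.

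Two further errors stand beside this one. The received treatment is called exogenous, whereas it is the regressor that needs an instrument. And those who received their allocated TSR are not the compliers: in the rTSR arm they include patients whose cuff would have led to rTSR under either allocation.

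At stake is the only analysis shown that addresses crossover, which the article lists among the trial's limitations and makes an objective of its internal pilot.

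**Working it through.** **Inputs from the Sample size and Primary outcome sections.** Target difference: "our target difference between the rTSR and aTSR groups is eight points". SD: "We also conservatively assumed a group SD of 25 points". Baseline/24-month correlation 0.35, power 90%, 5% significance (taken as two-sided), 182 per group, 15% loss to follow-up, 430 randomised. SPADI: "The total score ranges from 0 to 100".

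**Reproducing the plan's own figure.** The residual SD is 25 × √(1 − 0.35²). This gives 181 per arm against 182 stated, and 364 / 0.85 rounds up to 429 against 430. The inputs agree with the plan to within rounding. The plan states no figure for the CACE itself.

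**Formula.** With one binary instrument and no covariates, two-stage least squares is the Wald ratio: the ITT effect divided by the between-arm difference in the mean of the treatment variable. Covariate adjustment does not repair a wrong denominator. Let p_r and p_a be the proportions receiving their allocated implant in the rTSR and aTSR arms.

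- As written (received allocated TSR): denominator = p_r − p_a.
- Implant received (rTSR = 1), if all non-adherence is crossover: denominator = p_r − (1 − p_a) = p_r + p_a − 1.

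**Numbers.** The adherence rates are assumptions. The ITT effect is set at −8 (rTSR minus aTSR; a lower SPADI is better).

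| Adherence rTSR / aTSR | As written | With receipt of rTSR |
|---|---|---|
| 100% / 95% | −8 / 0.05 = −160 | −8 / 0.95 = −8.4 |
| 100% / 90% | −8 / 0.10 = −80 | −8 / 0.90 = −8.9 |
| 100% / 80% | −8 / 0.20 = −40 | −8 / 0.80 = −10.0 |
| 95% / 95% | −8 / 0: undefined | −8 / 0.90 = −8.9 |
| 95% / 98% | −8 / −0.03 = +267 | −8 / 0.93 = −8.6 |

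The inflation factor is (p_r + p_a − 1) / (p_r − p_a), which is 19, 9 and 4 in the first three rows. A mean difference on a 0 to 100 scale cannot exceed 100 in size, so the as-written estimate leaves the scale when 8 / gap > 100, that is, when the gap is below 0.08.

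**Simulation check.** There were 2,000 simulated trials per scenario, with 364 participants, SD 25, correlation 0.35, crossover unrelated to outcome and a true implant effect of −8. The expected ITT effect is then slightly under 8 in size. Median estimates as written were −156 (100/95), −71 (100/90) and −32 (100/80). With receipt of rTSR the median was −7.9 to −8.1 in every scenario. At 95/95 the as-written estimate had an interquartile range of −463 to +407 and the wrong sign in 49% of trials.

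**The exogenous label.** If the variable really were treated as exogenous, nothing would be left to instrument. The fit would be ordinary regression of SPADI on adherence. In the same simulations its median ran from +0.2 to +4.1, which is not a CACE either.

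**The complier definition.** Suppose 10% of participants have a cuff that would lead to rTSR whatever the allocation, and everyone else adheres. All 182 rTSR participants then received their allocated implant and count as compliers under the stated definition. Only about 0.90 × 182 = 164 of them would have received aTSR if allocated to it.

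**The case against.** The phrase may be loose drafting. Two-stage least squares with randomisation as the instrument is a standard design, and the authors may have meant the type of TSR received and written exogenous for endogenous. The article describes its analyses in brief and defers detail to a statistical analysis plan that is not shown. This rightly limits any claim about how the analysis will be run. It does not repair the rule as stated: the sentence on compliers supports the adherence reading, and nothing in the article corrects it.

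A reader might infer that the method must always produce an impossible number. The document does not support that. It gives no adherence rate, and at gaps of 10 to 20 percentage points an 8-point ITT effect gives 80 to 40 points, grossly inflated but on the scale. The undefined and sign-reversed cases need rTSR adherence equal to or below aTSR adherence. The Additional analyses section allows for that, but the crossover described under Interventions runs from aTSR to rTSR.

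A reader might also blame the exogenous label for the wrong denominator. It is a separate error; the adherence coding alone produces that denominator.

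Finally, this is one supplementary estimate. The primary comparison, the sample size, the secondary outcomes and the economic analysis do not depend on it. That stands, and it lowers the severity.

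**Conclusion.** The analysis as written does not estimate a CACE. Its first stage is the adherence gap between two active arms, so the ITT effect is inflated about 19-fold, 9-fold and 4-fold at gaps of 5, 10 and 20 percentage points, relative to the estimate using receipt of rTSR. These factors rest on assumed adherence rates, full adherence in the rTSR arm and all non-adherence being crossover. For an 8-point ITT effect, the result exceeds the SPADI range only when the gap is below about 8 percentage points. It is undefined when adherence is equal and changes sign if rTSR adherence is the lower. The exogenous label and the complier definition are wrong whatever the rates.

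This should be fixed before analysis. It does not threaten the primary result, but it leaves the trial without a valid stated analysis of crossover.

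**What to change.** Reword the CACE paragraph, and carry the wording into the statistical analysis plan:

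- The endogenous variable is the implant received (rTSR = 1, aTSR = 0), instrumented by randomised allocation. Age, gender and baseline total SPADI enter both stages as exogenous covariates.
- Compliers are participants who would receive whichever implant they were allocated.
- State how participants with no TSR are coded, because a single rTSR indicator would count them with aTSR. This is secondary detail that the statistical analysis plan can carry.

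The cost is wording only. The article already provides for recording the implants used in both arms, and the statistical analysis plan is to be agreed before data collection ends.

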#### Missing data

The primary analysis model assumes missing outcome data are missing at random (MAR) and uses full information maximum likelihood to implicitly handle missing outcome data. It is expected that other covariates included in the model, for example, gender, are unlikely to be missing. Therefore, as it is unlikely to have a large proportion of missingness in the analysis, multiple imputation will not be performed as part of the primary analysis. However, it is possible that participants who failed to complete their follow-ups will differ from those who did (for example, had worse pain/disability following surgery and therefore would have scored higher on the SPADI if they had completed the follow-up). This would suggest the data were missing not at random and represent a departure from the MAR assumption. Additional sensitivity analyses will be conducted using a pattern-mixture model to examine how sensitive the primary treatment effect estimate is to an assumption that (a) all of these missing observations (if present) are poor outcomes in the SPADI, and conversely that (b) all of these missing observations are beneficial outcomes in the SPADI, and thereby modelling ‘best case’ and ‘worst case’ scenarios for the primary outcome analysis.

While the results of this sensitivity analysis will not be directly comparable to the primary analysis model, it will be able to give an indication of how sensitive the estimate of the treatment effect is to departures from the MAR assumption in the primary outcome data.

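### The missing-not-at-random scenarios move all missing SPADI scores in one direction without regard to arm, so they are best and worst cases for the mean score and do not bound the treatment difference

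*Protocol article*

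**What the plan says.** The primary comparison is the between-group difference in SPADI at 24 months, taken from a constrained longitudinal model (Statistical methods, Primary outcome). That model assumes outcomes are missing at random. The Missing data section accepts that non-responders may differ from responders, for example by having worse pain or disability, and plans a pattern-mixture sensitivity analysis of the treatment effect estimate. The analysis has two scenarios: (a) "all of these missing observations (if present) are poor outcomes in the SPADI" and (b) "all of these missing observations are beneficial outcomes in the SPADI". The section describes the pair as modelling best and worst cases for the primary outcome analysis. It adds that "the results of this sensitivity analysis will not be directly comparable to the primary analysis model", but expects them to indicate how sensitive the treatment effect is to departures from missing at random.

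The Sample size section plans for 15% loss to follow-up at 24 months, as one overall figure with no split by arm. The Statistical methods section says the analyses are described in brief and that a full statistical analysis plan will follow.

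**The concern.** A best case and a worst case for a treatment comparison should be the assumptions that move the difference furthest in each direction. For a two-arm difference, these set the missing outcomes poor in one arm and good in the other. The two stated scenarios set them poor everywhere, or good everywhere. That gives the extremes of the overall mean SPADI. For the difference, a change in one arm is offset wholly or partly by the same change in the other.

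At stake is the robustness statement that will accompany the primary result. The departure most relevant to a comparison is one in which non-responders do worse in one arm than in the other, and no stated scenario isolates it. The article gives grounds for thinking it possible. The Background section reports revision for cuff failure at 0.42 per 100 prosthesis years for anatomic and 0.02 for reverse replacement. It also reports that glenoid loosening was more common with the anatomic implant and that scapular notching occurred only with the reverse. If failure modes differ by implant, the reasons for non-response may differ too.

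**Working it through.** **Inputs.** From Sample size: target difference 8 points, SD 25, baseline/24-month correlation 0.35, 90% power, 5% significance level (taken as two-sided), 182 per group, 15% loss, 430 randomised. From Primary outcome (Outcomes): SPADI runs from 0 (best) to 100 (worst). Assumptions: the missing fractions by arm, the size of the offset d, and, for fixed-value imputation, observed means of 22 (rTSR) and 30 (aTSR).

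**The plan's own figure.** n per arm = 2 × (1.960 + 1.282)² × 25² × (1 − 0.35²) / 8² = 180.1, so 181, against 182 stated. Power at 182 is 90.3%. 364 / 0.85 = 428.2, so 429, against 430 stated. The inputs reproduce. They imply SE = 25 × √(1 − 0.35²) × √(2/182) = 2.45.

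**Additive offsets.** Let p_r and p_a be the missing fractions and d_r and d_a the departures from missing at random. The rTSR minus aTSR difference changes by p_r·d_r − p_a·d_a. With a common offset d, this is d·(p_r − p_a).

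| Missing rTSR / aTSR | d | Same direction in both arms | One arm only | Opposite directions |
|---|---|---|---|---|
| 15% / 15% | 10 | 0.0 | ±1.5 | ±3.0 |
| 15% / 15% | 20 | 0.0 | ±3.0 | ±6.0 |
| 12% / 18% | 20 | ±1.2 | ±2.4 (rTSR), ±3.6 (aTSR) | ±6.0 |
| 10% / 20% | 25 | ±2.5 | ±2.5 (rTSR), ±5.0 (aTSR) | ±7.5 |

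With equal missingness, the same-direction scenarios leave the difference unchanged whatever the size of d. At 10% v 20% they reach one third of the opposite-direction change.

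**One fixed value imputed.** Estimated difference = [(1 − p_r)·22 + p_r·v_r] − [(1 − p_a)·30 + p_a·v_a], starting from −8.

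- 15% in each arm, all 100: (18.7 + 15) − (25.5 + 15) = −6.8. All 0: 18.7 − 25.5 = −6.8. Both scenarios give the same estimate.
- 15% in each arm, opposite assignment: 18.7 − 40.5 = −21.8, and 33.7 − 25.5 = +8.2.
- 10% / 20%: all 100 gives 29.8 − 44 = −14.2 and all 0 gives 19.8 − 24 = −4.2. Opposite assignment gives −24.2 and +5.8.

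**Standard error under a fixed value** (215 per arm, 15% missing in each). Per-arm variance given baseline = 0.85 × 625 + 0.15 × 0.85 × (mean − v)² − (0.85 × 0.35 × 25)², where the last term is 55.3.

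- v = 100: aTSR 531.3 + 624.8 − 55.3 = 1100.7; rTSR 531.3 + 775.7 − 55.3 = 1251.6. SE = √(2352.3/215) = 3.31, so z = 6.8/3.31 = 2.06 (p = 0.04).
- v = 0: aTSR 531.3 + 114.8 − 55.3 = 590.7; rTSR 531.3 + 61.7 − 55.3 = 537.6. SE = √(1128.3/215) = 2.29, so z = 2.97.
- Observed difference 7 (rTSR mean 23) with v = 100: 5.95/3.29 = 1.81 (p = 0.07). Observed difference 6 (rTSR mean 24): 5.1/3.28 = 1.55 (p = 0.12).

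The SE therefore rises well above 2.45 in scenario (a) with an extreme poor value. It does not rise in scenario (b) on these assumptions, because 0 lies nearer the observed means.

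**Tipping point, additive offset, SE held at 2.45, 15% missing in each arm.** For an observed difference of 8, significance is lost at (8 − 1.96 × 2.455)/0.15 = 21.3 points in one arm, or at 3.19/0.30 = 10.6 points in opposite directions. For an observed difference of 6 (illustrative), a one-arm offset of (6 − 4.81)/0.15 = 7.9 points is enough.

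**The case against.** First, exact cancellation is conditional. It needs an additive offset of the same size in both arms and equal missing fractions, and the article gives no loss by arm. With unequal loss, a shift of d·(p_r − p_a) remains. This stands: a reader who inferred that the shifts always cancel, or that nothing is tested, would be going beyond the document.

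Second, the wording fits assigning a poor value at least as well as adding an offset. On that reading scenario (a) attenuates the estimate and, with an extreme value, inflates its standard error. An observed difference of 6 or 7 would lose significance when missing scores are set to 100. This also stands, so a reader should not infer that the analysis cannot fail. What it tests under equal missingness is dilution and added variance, not a departure that differs by arm.

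Third, the section does not say in words that both arms are treated alike, and the unseen statistical analysis plan may define offsets by arm. It therefore cannot be said that the trial will never examine arm-specific departures. But the article does more than leave detail open: it defines two scenarios without reference to arm and attaches a label that they do not support.

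Fourth, the consequence may be modest. A 10-point offset in one arm moves the effect by 1.5 points, and a difference of 8 is overturned only by a one-arm offset of about 21 points. Participants are blinded, and reminders and an 18-month SPADI are meant to limit loss. This bears on how serious the point is, not on whether the scenarios bound the effect. The admitted lack of comparability with the primary model is a disclosed limitation and not a further error.

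**Conclusion.** The point holds on the plain reading of the Missing data section. The two scenarios are extremes for the level of SPADI. They do not bound the between-group difference when both arms have missing data.

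At 15% missing in each arm, an additive 20-point offset applied to everyone moves the effect by 0.0. The same offset moves it by 3.0 points in one arm only and by 6.0 in opposite directions, against a target of 8. At 12% v 18% the stated scenarios move it by 1.2. With fixed values of 0 or 100 and equal missingness, both scenarios give 6.8 in place of 8, whereas opposite assignment runs from 21.8 in favour of rTSR to 8.2 in favour of aTSR.

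These figures rest on assumed missing fractions by arm, assumed offsets and, for fixed values, assumed means of 22 and 30. The primary estimate and its model are not affected. The weakness lies in the claim of robustness attached to them.

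**What to change.** In the Missing data section and the statistical analysis plan, keep scenarios (a) and (b) and add arm-specific ones: offsets in rTSR only, in aTSR only, and in opposite directions (poor in one arm, beneficial in the other). Apply them to the missing 24-month SPADI over a stated range, for example 0 to 20 points in each direction, on the scale of the primary model, so that the results can be read beside the primary estimate. State whether a departure is an additive offset or an assigned value. Then either report the offset at which the conclusion changes or drop the best-case and worst-case label. If the statistical analysis plan already defines offsets by arm, aligning the article's wording with it is enough. The cost is some wording and a little more analysis time; no new data are needed.

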#### Primary outcome

The primary comparison of interest is the between-groups difference in SPADI score at 24 months. The estimate for this difference will be derived from a constrained longitudinal data analysis model.^43^ This will be a linear mixed-effects model, featuring SPADI score at baseline, 3-, 6-, 12-, 18- and 24-months post-randomisation as the outcome, intervention group, timepoint, age and gender as fixed effects, and participant identifier and trial site as random effects. A series of group-by-time point interaction effects will be included as fixed effects, thereby making no assumptions about the shape of the SPADI score trajectory over time. The model will be constrained so that the baseline SPADI scores are equal between groups.^43^ The model will use maximum likelihood estimation, with an unstructured covariance matrix. The between-groups difference in SPADI score at 24 months will be extracted from this model as the primary outcome and reported with a 95% CI and p value.

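### The missing-not-at-random check on the primary SPADI result is planned as not directly comparable with the primary model, so it gives only a rough indication of dependence on missing at random

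*Protocol article*

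**What the plan says.** Under Statistical methods, Primary outcome, the article says of the 24-month between-group contrast: "The estimate for this difference will be derived from a constrained longitudinal data analysis model". That model uses every occasion, "featuring SPADI score at baseline, 3-, 6-, 12-, 18- and 24-months post-randomisation as the outcome", with age and gender as fixed effects and participant and site as random effects.

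Under Missing data, the same model is the basis for handling dropout: "The primary analysis model assumes missing outcome data are missing at random (MAR) and uses full information maximum likelihood". The section accepts that non-completers may have done worse and adds sensitivity analyses "using a pattern-mixture model to examine how sensitive the primary treatment effect estimate is to an assumption that" either "all of these missing observations (if present) are poor outcomes in the SPADI" or, conversely, "all of these missing observations are beneficial outcomes in the SPADI".

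The closing sentence of the section has two halves. The first concedes that "the results of this sensitivity analysis will not be directly comparable to the primary analysis model". The second adds that "it will be able to give an indication of how sensitive the estimate of the treatment effect is to departures from the MAR assumption". The article does not give the reason for the non-comparability, the model to be fitted, or whether a scenario applies to both arms alike.

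**The concern.** A sensitivity analysis isolates one assumption when everything else is held fixed. Here the target is the primary estimate, yet the plan accepts in advance that the result cannot be set directly beside it. If the reason is a different estimator, for example one that does not use the 3- to 18-month scores, then the result with no departure from MAR is not the primary estimate. Any difference would then combine a change of model with a change of missing-data assumption.

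A shift due to the estimator could be read as evidence against MAR, or could partly cancel a real departure and look like robustness. The plan allows for 15% loss to follow-up and itself offers a plausible reason why the missing scores might be worse.

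**Working it through.** **1. The plan's own figures.** The inputs from Sample size are a target difference of 8, SD 25, baseline/24-month correlation 0.35, 90% power, a 5% level (two-sided assumed) and 15% loss.
- Adjusted SD = 25 × √(1 − 0.35²) = 23.42.
- n per arm = 2 × (1.960 + 1.282)² × 23.42² / 8² = 180.1, so 181. The plan states 182, and power at 182 is 90.3%.
- 364 / 0.85 = 428.2, so 429. The plan states 430.

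These agree, so 215 per arm, SD 25, correlation 0.35 and about 15% missing serve as the inputs below.

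**2. What a difference would contain.** Let P be the primary estimate and S(δ) the sensitivity estimate with shift δ applied to the missing scores. Then

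S(δ) − P = [S(δ) − S(0)] + [S(0) − P].

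The first bracket is the effect of the missing-data assumption. The second is the change of model. If the primary model is kept, the second bracket is zero (within simulation error) and the first is, to first order, δ_rTSR × m_rTSR − δ_aTSR × m_aTSR, where m is the share missing in each arm.

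**3. Size of the second bracket.** The sensitivity model is not stated. As an assumption, take it to be a 24-month ANCOVA on observed cases, adjusted for baseline, with true effect −8 and no shift. The follow-up correlations and dropout mechanisms are also assumptions. The SD is that of the gap between the two estimates from the same data, across simulated trials.

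| Missingness (no departure from MAR) | Correlation between follow-up scores | Mean gap | SD of gap |
|---|---|---|---|
| Purely random | 0.75 or 0.85 per 6 months | about 0 | 0.7 to 0.8 |
| Depends on 18-month score, alike in both arms | 0.75 or 0.85 per 6 months | about 0 to 0.15 | 0.8 to 0.9 |
| As above, about 14% missing | 0.7 between all visits | −7.78 − (−8.07) = 0.29 | 0.8 |
| Depends on 18-month score in aTSR, random in rTSR, 15% | 0.75 / 0.85 per 6 months | −6.34 − (−7.99) = 1.65 / −6.11 − (−8.04) = 1.93 | not recorded |
| As above, 20% v 10% missing | 0.75 / 0.85 per 6 months | −5.77 − (−8.01) = 2.24 / −5.42 − (−8.00) = 2.58 | not recorded |

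Steeper one-arm selection (log-odds 1.5 per SD) raised the last two rows to 2.8 to 3.2 and 3.6 to 4.2 points. In the third row the standard error of the primary-type estimate was 2.33, so a gap SD of 0.78 is about a third of it (0.78 / 2.33 = 0.33).

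**4. Size of the first bracket, for scale.**
- A 10-point shift in one arm with 15% missing: 10 × 0.15 = 1.5 points.
- Missing scores set to the scale ends, with assumed means of 30 (aTSR) and 22 (rTSR), alike in both arms and 15% missing in each. All poor: (0.85 × 22 + 0.15 × 100) − (0.85 × 30 + 0.15 × 100) = 33.7 − 40.5 = −6.8. All beneficial: 18.7 − 25.5 = −6.8. Either way the effect moves 1.2 points from −8.
- The same, with 10% missing in aTSR and 20% in rTSR: 37.6 − 37.0 = +0.6 (all poor) and 17.6 − 27.0 = −9.4 (all beneficial).
- Opposite scenarios by arm, 15% missing in each: +8.2 to −21.8.

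A model gap with SD 0.7 to 0.9 is therefore not negligible against movements of 1.2 to 1.5 points. It is small against movements of 8 points or more.

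**The case against.** A reader might infer that the plan contradicts itself, or that the analysis cannot show anything about MAR. The text supports neither. The sentence that concedes non-comparability goes on to claim only an indication of sensitivity, and a result that is not directly comparable can still inform.

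The change of estimator is also an inference. The article does not say that interim scores are dropped or that an ANCOVA is used. The caveat may mean only that estimates under deliberately extreme assumptions should not be read beside the MAR estimate. The article describes its methods in brief and leaves the detail to the SAP, so the absence of a named model is not a fault.

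Further, the all-poor and all-beneficial scenarios sit within one analysis, so their contrast with each other involves no change of model. The larger gaps in the working, 1.65 points and above, need outcome-dependent dropout in one arm only.

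Most of this stands and limits the point. What remains is that the article positively states the non-comparability, so this is more than detail left for later, and the limitation is avoidable because a pattern-mixture analysis can be anchored to the primary model. The contrast between the two scenarios is only a partial substitute: applied alike in both arms with equal missingness, both give −6.8 and the contrast is zero. How the scenarios are assigned to arms is a separate matter.

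**Conclusion.** The point holds as an avoidable weakness in the only MAR check described for the primary outcome. It is not a flaw in the primary analysis, and it does not make the check worthless. As planned, the check gives a rough indication; a difference from the primary estimate cannot be cleanly attributed to the missing-data assumption if the model changes too.

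If the sensitivity model were a 24-month ANCOVA on observed cases, the change of model alone would give a mean gap of about 0 to 0.3 points, with an SD of about 0.7 to 0.9, when missingness is random or selection is alike in both arms. The mean gap would be larger only if outcome-dependent dropout differed by arm. All of these sizes rest on the assumed sensitivity model and the assumed follow-up correlations, neither of which is in the article.

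**What to change.** Run the missing-not-at-random scenarios on the primary model. One way is to:
- impute missing SPADI scores under MAR from the constrained longitudinal model, using all visits, age, gender and site;
- shift only the imputed 24-month values;
- refit the same model and pool the results by Rubin's rules.

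Include a zero-shift run, require it to reproduce the primary estimate within simulation error, and report each scenario as a change from that anchor. Other implementations would serve if they keep the model fixed and meet the zero-shift requirement.

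Replace the comparability sentence with a statement that the sensitivity analyses use the primary model and differ from it only in the values assumed for missing 24-month scores.

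The cost is a sentence or two in the protocol or SAP and modest extra programming and run time. No new data or participants are needed. The article has the SAP agreed before data collection ends, so the change can be made there.
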